### Study Outcomes

The primary outcome is the change in pain intensity, measured using the VAS, from baseline (T0) to 60 days (T1) following multidisciplinary committee assessment. A reduction of at least 1 point on the VAS was predefined as the minimal clinically important difference, based on previous literature in patients with cancer-related pain [31]. This threshold was used for the sample size calculation and will also serve to interpret the clinical relevance of the observed changes.

Secondary outcomes include changes between T0 and T1 in health-related quality of life measured using the EQ-5D [32], pain-related functional interference assessed with the Brief Pain Inventory–Short Form (BPI-SF) [33], DMED, analgesic treatment–related adverse effects, and PREMs, including satisfaction with care assessed using a Likert-scale questionnaire at T1.

Table 2 summarizes the study outcomes, instruments, and time points. The primary analysis will focus on paired comparison of VAS scores between T0 and T1. Secondary outcomes listed in Table 2 will be analyzed accordingly based on variable type and distribution.

**Table 2 table2:** Study outcomes.

Outcome category	Variable	Instrument or source	Time points	Type
Pain intensity	VAS^a^ score (0-10)	VAS	T0 and T1	Primary
Quality of life	EQ-5D index score	EQ-5D questionnaire	T0 and T1	Secondary
Pain interference	BPI-SF^b^ interference score	BPI-SF	T0 and T1	Secondary
Opioid consumption	Daily morphine equivalent dose (mg/day)	Clinical record	T0 and T1	Secondary
Adverse effects	Presence or absence and type	Clinical assessment	T0 and T1	Secondary
Committee recommendation	Type of recommendation issued	Committee record	T0	Descriptive
Implementation of recommendations	Implementation status (implemented, partially implemented, or not implemented)	Electronic medical record	T1	Exploratory
Patient satisfaction	Likert-scale satisfaction score	PREM^c^ questionnaire	T1	Secondary

^a^VAS: visual analog scale.

^b^BPI-SF: Brief Pain Inventory–Short Form.

^c^PREM: patient-reported experience measure.

### Recruitment and Study Procedures

#### Patient Eligibility Criteria

##### Inclusion Criteria

Inclusion criteria include adults aged ≥18 years with active cancer, defined as histologically confirmed malignant disease receiving active antineoplastic treatment or with documented disease progression; moderate to severe cancer-related pain (VAS ≥4); presentation to the multidisciplinary cancer pain management committee; ability to understand study procedures in Spanish or Galician; and provision of written informed consent.

##### Exclusion Criteria

Exclusion criteria include patients with severe cognitive impairment, dementia, intellectual disability, or any other condition preventing reliable completion of study assessments; patients in the agonal phase or with an expected survival insufficient to complete follow-up; refusal or inability to provide written informed consent.

#### Recruitment

All eligible patients meeting the inclusion criteria and none of the exclusion criteria will be consecutively invited to participate in the study. Referral to the multidisciplinary cancer pain management committee may be initiated by any physician involved in the care of adult patients with cancer. Referrals are most commonly made by specialists in medical oncology, radiation oncology, pain medicine, hematology, palliative care, or other hospital-based specialties managing patients with cancer. Referral is made at the treating physician’s discretion whenever multidisciplinary assessment is considered clinically appropriate. The multidisciplinary committee meets once monthly, and each meeting lasts approximately 1 hour. Clinical cases are presented by the referring physician and discussed by a multidisciplinary panel, including specialists in pain medicine, medical oncology, radiation oncology, and pain nursing. Additional specialists may participate whenever considered clinically appropriate. Management recommendations are established by multidisciplinary consensus after review of the patient’s oncological history, pain characteristics, current oncological treatment, previous analgesic strategies, imaging findings when available, and overall clinical condition. Recommendations may include optimization of pharmacological therapy, opioid rotation or dose adjustment, interventional pain procedures, referral for radiotherapy, referral to other medical specialties, psycho-oncology assessment, rehabilitation, palliative care interventions, or additional diagnostic evaluation according to individual patient needs. Implementation of committee recommendations will be assessed by reviewing the patient’s electronic medical record during follow-up and categorized as fully implemented, partially implemented, or not implemented. Written informed consent will be obtained by the principal investigator during the first face-to-face visit to the pain unit after multidisciplinary committee evaluation. For hospitalized patients, informed consent will be obtained during a bedside visit following committee discussion. Patients will be informed that participation is entirely voluntary and that declining participation or withdrawing from the study will not affect their routine clinical care or any therapeutic decisions made by the multidisciplinary committee. Baseline assessments (T0) will be completed as close as possible to multidisciplinary committee assessment, according to routine clinical practice. Participants will subsequently be followed for 60 days, with the primary end point assessed at T1. Figure 1 summarizes the participant flow throughout the study.

**Figure 1 figure1:**
[figure not shown]
Planned participant flow for the prospective observational pre-post study. BPI-SF: Brief Pain Inventory–Short Form; PREM: patient-reported experience measure; VAS: visual analog scale.

#### Data Management and Security

Clinical data will be collected using a study-specific electronic case report form. All data will be coded and pseudonymized to protect participant identity. Identifiable personal data will be stored separately from clinical data and secured in locked facilities within the responsible health care institution, with access restricted to authorized members of the research team. Only the research team and competent health authorities, who are bound by confidentiality obligations, will have access to the study data. Data processing, storage, communication, and transfer will be carried out in accordance with the General Data Protection Regulation (Regulation (EU) 2016/679) and relevant national data protection laws. The health care institution where data are collected will act as the data controller. Upon completion of the study, data will be anonymized for future research use when participants have provided explicit consent; otherwise, the data will be securely destroyed.

### Data Monitoring

Given the observational nature of the study and the absence of experimental interventions, no independent data monitoring committee was established. Data quality will be reviewed monthly by the principal investigator according to a predefined quality control checklist to verify completeness, internal consistency, and accuracy of data entry. Any discrepancies identified during quality control procedures will be resolved through review of the original clinical records before database locking.

### Statistics

#### Sample Size and Power Calculations

The sample size calculation was based on the primary outcome, defined as the change in VAS score between baseline and 60 days. The calculation was based on a paired comparison of means. A reduction of at least 1 point on the VAS was considered clinically relevant. Assuming a significance level of 5% (α=.05), a statistical power of 80% (β=.20), and an SD of 2, a total of 64 patients would be required to detect statistically significant differences. Allowing for an anticipated 5% dropout rate, a total sample size of 68 patients will be recruited.

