#### Statistical Analysis Plan

Statistical analyses will be performed using SPSS (IBM Corp) or equivalent statistical software. Baseline demographic and clinical characteristics will be summarized using appropriate descriptive statistics. Variables of interest will include age, sex, cancer type, tumor stage, presence of metastatic disease, ongoing oncological treatment, baseline opioid use (DMED), previous interventional pain procedures, and palliative care status. A 2-sided *P* value of <.05 will be considered statistically significant. Given the exploratory nature of secondary outcomes, no formal adjustment for multiple comparisons will be applied; therefore, secondary analyses will be interpreted cautiously.

Categorical variables will be summarized as frequencies and percentages. Continuous variables will be described using means and SDs or medians and IQRs, depending on data distribution.

Normality of continuous variables will be assessed using the Shapiro-Wilk test to determine the appropriate statistical test.

For the primary outcome, VAS scores at baseline (T0) and at 60 days (T1) will be compared using paired *t* tests or Wilcoxon signed rank tests, as appropriate. Mean changes in VAS scores will be reported together with 95% CIs and standardized effect sizes (Cohen *d*) to facilitate interpretation of both statistical and clinical significance.

Secondary pre-post comparisons for continuous variables (eg, EQ-5D scores, BPI-SF scores, and DMED) will be analyzed using the same approach. Categorical variables, including adverse effects and selected PREMs, will be analyzed using chi-square or McNemar tests, as appropriate. Because pain outcomes may be influenced by patient and disease characteristics, exploratory multivariable regression analyses will be performed to evaluate the association between multidisciplinary committee assessment and changes in pain intensity after adjustment for clinically relevant covariates. Prespecified candidate covariates will include age, sex, cancer type, tumor stage, metastatic disease, baseline VAS score, baseline opioid consumption, ongoing oncological treatment, interventional pain procedures, and palliative care status.

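### The stated sample size of 64 does not follow from the stated paired inputs, which give 34 pairs; the error is conservative and the SD needs a label

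*Protocol article*

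**What the plan says.** The section Sample Size and Power Calculations names the quantity being sized: "The sample size calculation was based on the primary outcome, defined as the change in VAS score between baseline and 60 days". It names the method: "The calculation was based on a paired comparison of means". It sets the difference: "A reduction of at least 1 point on the VAS was considered clinically relevant". With 5% significance and 80% power it then reports the result: "an SD of 2, a total of 64 patients would be required to detect statistically significant differences". A 5% dropout allowance raises 64 to 68.

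The Statistical Analysis Plan section makes the test two-sided ("A 2-sided *P* value of <.05 will be considered statistically significant") and names a paired t test or a Wilcoxon signed rank test for VAS at T0 against T1. Strengths and Limitations confirms that there is no control group. The SD is not labelled as that of the change or that of a score at one time point, and no correlation between T0 and T1 is given.

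Of the 1-point difference, Study Outcomes says: "This threshold was used for the sample size calculation and will also serve to interpret the clinical relevance of the observed changes".

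**The concern.** One paragraph gives the method, every numerical input and the answer, so the answer can be checked directly. At a difference of 1 and an SD of 2 the standardized difference is 0.5. For that value, 64 is a familiar number, but it is the size of each group in a two-group comparison. This study has one cohort measured twice.

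At stake is the only quantitative justification for the recruitment target. If it does not follow from its inputs, a reader cannot tell what the design can detect: 80% power for 1 point, as stated, or something quite different. An unseen full plan cannot settle this. If it holds a different SD or a correlation, the article still misreports the calculation.

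**Working it through.** **Inputs.** Difference 1 VAS point, SD 2, alpha .05, power 80%, paired comparison on the change, dropout 5% (Sample Size and Power Calculations); two-sided test (Statistical Analysis Plan).

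**1. Stated method, with SD of the change = 2.**
- Normal approximation: n = ((z₀.₉₇₅ + z₀.₈₀) × SD / difference)² = ((1.960 + 0.842) × 2 / 1)² = 31.4, so 32.
- Paired t test (noncentral t, n − 1 degrees of freedom, noncentrality 0.5√n): 33.4, so 34.
- After 5% dropout: 34 / 0.95 = 35.8, so 36.

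The stated 64 is not reproduced.

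**2. Other settings of the paired calculation, SD of the change still 2.**

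| Setting | Pairs |
|---|---|
| One-sided, 80% power | 27 |
| Two-sided, 90% power | 44 |
| Two-sided, 95% power | 54 |
| Two-sided, 80% power, inflated for Wilcoxon | about 36 to 39 |

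None reaches 64.

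**3. What does give 64.** Two independent samples at d = 1/2 = 0.5, two-sided .05, 80% power: 63 per group by normal approximation; 63.8, so 64 per group, by the t test.

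**4. Reading 2 as the SD at each time point.** The SD of the change is then 2 × √(2(1 − ρ)), where ρ is the T0–T1 correlation. The documents give no ρ, so a range is shown.

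| ρ (assumed) | SD of change | Pairs for 80% power | Power at 64 pairs |
|---|---|---|---|
| 0 | 2.83 | 65 | 79.5% |
| 0.2 | 2.53 | 53 | 87.6% |
| 0.3 | 2.37 | 46 | 91.5% |
| 0.5 | 2.00 | 34 | 97.6% |
| 0.7 | 1.55 | 21 | 99.9% |

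Only ρ = 0 comes near 64. There the variance of the change is the sum of the two separate variances, as in the unpaired formula, and pairing gains nothing.

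**5. What the planned numbers deliver if the SD of the change is 2.**
- Power for 1 point: 97.6% at 64 pairs, 98.2% at 68.
- Change detectable with 80% power at 64 pairs: 0.71 points.
- 95% CI half-width at 64 pairs: t₀.₉₇₅,₆₃ × 2/√64 = 2.00 × 0.25 = 0.50 points.

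**6. Dropout step.** 64 / 0.95 = 67.4, so 68. This is correct.

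**The case against.** The strongest defence is that the SD is unlabelled. If 2 is the SD of a single VAS score and the authors deliberately assumed no correlation as a worst case, a paired calculation gives 65 by the t test or 63 by normal approximation, close to 64. The documents cannot rule this out. Nor can a near-zero correlation be dismissed from them: entry at VAS ≥4 restricts the baseline range, and treatment changes during follow-up may weaken the link between the two scores. This stands in part. It means that use of a two-sample formula cannot be stated as fact. It does not rescue the paragraph, which mentions neither a single-time-point SD nor a correlation and names the change as the quantity sized.

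A second defence is that the discrepancy does no harm. The study observes routine care, and a larger number exposes no one to additional treatment. This also stands, and it limits the consequence to the accuracy of the stated justification.

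Two stronger readings are tempting.
- A reader might infer that a result with P<.05 will be taken as proof of a 1-point change, since about 0.50 points is already significant at 64 pairs with SD 2. The documents do not support this. Study Outcomes keeps the 1-point threshold for judging clinical relevance, and the Statistical Analysis Plan section reports the mean change with its 95% CI and Cohen d. Significance below the design difference also occurs in correctly sized studies.
- A reader might infer that, since 34 is half of 68, a 50% loss would be tolerable. That holds for power only, and only if the SD of the change is 2; at 2.83, 34 completers give about 52% power. The Statistical Analysis Plan section also warns that missing outcomes may be informative, so bias would remain whatever the power.

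**Conclusion.** The point holds as a failure to reproduce. With the SD read as that of the change, which is what the paragraph says is being sized, the requirement is 34 pairs (36 with dropout) against 64 stated, and power at 64 is about 97.6% against 80% stated. With the SD read as that of a single score, 64 is roughly right only at zero correlation (65 pairs; 79.5% power at 64); any positive correlation lowers the requirement.

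The error is therefore conservative. A reader might conclude that the study is too small or the primary test compromised; neither reading supports that. What is wrong is that the stated method, SD, power and number do not belong together. These figures rest on the t test with two-sided .05 and a 1-point difference. The origin of 64 in a two-sample formula remains an inference from the numerical match.

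**What to change.** Keep the recruitment target of 68. In Sample Size and Power Calculations, state whether 2 is the SD of the within-patient change or the SD at one time point; if the latter, give the assumed T0–T1 correlation. Then restate the result to match. If it is the SD of the change, for example: *assuming an SD of the within-patient change of 2, 34 completers give 80% power for a 1-point change; 64 completers give about 98% power and a 95% CI half-width of about 0.5 points.* If it is a single-time-point SD, report the number and power for the stated correlation, as in the second table above.

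The text should not offer a tolerable level of loss, and no added sentence on clinical relevance is needed.

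The cost is one reworded paragraph and a note on the registration. Patients, procedures and analysis do not change. With 3 participants enrolled at submission, the correction can be made well before any outcome analysis.

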#### Statistical Analysis Plan

Statistical analyses will be performed using SPSS (IBM Corp) or equivalent statistical software. Baseline demographic and clinical characteristics will be summarized using appropriate descriptive statistics. Variables of interest will include age, sex, cancer type, tumor stage, presence of metastatic disease, ongoing oncological treatment, baseline opioid use (DMED), previous interventional pain procedures, and palliative care status. A 2-sided *P* value of <.05 will be considered statistically significant. Given the exploratory nature of secondary outcomes, no formal adjustment for multiple comparisons will be applied; therefore, secondary analyses will be interpreted cautiously.

Categorical variables will be summarized as frequencies and percentages. Continuous variables will be described using means and SDs or medians and IQRs, depending on data distribution.

Normality of continuous variables will be assessed using the Shapiro-Wilk test to determine the appropriate statistical test.

For the primary outcome, VAS scores at baseline (T0) and at 60 days (T1) will be compared using paired *t* tests or Wilcoxon signed rank tests, as appropriate. Mean changes in VAS scores will be reported together with 95% CIs and standardized effect sizes (Cohen *d*) to facilitate interpretation of both statistical and clinical significance.

Secondary pre-post comparisons for continuous variables (eg, EQ-5D scores, BPI-SF scores, and DMED) will be analyzed using the same approach. Categorical variables, including adverse effects and selected PREMs, will be analyzed using chi-square or McNemar tests, as appropriate. Because pain outcomes may be influenced by patient and disease characteristics, exploratory multivariable regression analyses will be performed to evaluate the association between multidisciplinary committee assessment and changes in pain intensity after adjustment for clinically relevant covariates. Prespecified candidate covariates will include age, sex, cancer type, tumor stage, metastatic disease, baseline VAS score, baseline opioid consumption, ongoing oncological treatment, interventional pain procedures, and palliative care status.

Because of the observational design, the relatively small sample size, and the exploratory nature of these analyses, adjusted regression models will be considered hypothesis-generating and interpreted with appropriate caution. Predefined exploratory subgroup analyses will be performed whenever sample size permits. These analyses may include comparisons according to cancer type, metastatic vs nonmetastatic disease, baseline pain severity (moderate vs severe), and patients who are receiving palliative vs nonpalliative care. These subgroup analyses will be considered exploratory and interpreted cautiously.

Analyses will primarily be conducted using complete-case analysis. The frequency, pattern, and potential reasons for missing data will be described. In patients with advanced cancer, missing outcome data may result from clinical deterioration, hospitalization, or death and may therefore be informative (missing not at random). If missing data for the primary outcome exceed 5%, multiple imputation will be considered only as part of sensitivity analyses and only if the missing-data mechanism is considered reasonably compatible with the missing-at-random assumption. The results of any imputation-based analyses will be interpreted cautiously in light of the potential for informative missingness. Additional sensitivity analyses, including complete-case analyses, will be performed whenever appropriate to assess the robustness of the primary findings. All analyses will follow the predefined statistical plan approved by the research ethics committee.

As this is an observational study protocol rather than a clinical trial, the manuscript was primarily prepared in accordance with the STROBE (Strengthening the Reporting of Observational Studies in Epidemiology) statement [34]. Elements of the SPIRIT (Standard Protocol Items: Recommendations for Interventional Trials) statement were considered where applicable to improve protocol transparency [35].

A participant flow diagram will be used to describe progression through the study, including numbers assessed for eligibility, enrolled, completing follow-up, and included in the final analysis.

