#### Recruitment and Informed Consent

Patients meeting the eligibility criteria are invited to participate by the principal investigator during the first face-to-face visit to the pain unit following committee discussion. Written informed consent is obtained before study-specific data collection.

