### Strengths and Limitations

Strengths of this protocol include its prospective observational design, prospective protocol registration, consecutive patient recruitment, standardized outcome assessment, and evaluation of both clinical and patient-reported outcomes under routine clinical conditions. Furthermore, the multidisciplinary nature of the committee reflects contemporary recommendations for the management of complex cancer-related pain.

Several limitations should also be acknowledged. Because of the observational pre-post design and the absence of a control group, causal inference regarding the effect of multidisciplinary committee assessment cannot be established. Changes in pain intensity may also be influenced by regression to the mean, the natural course of the underlying disease, disease progression or response to oncological treatment, medication adjustments, or other concurrent clinical interventions occurring during follow-up. In addition, the single-center design may limit external validity, and residual confounding cannot be completely excluded despite planned exploratory adjusted analyses.

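### The exploratory regression names committee assessment as its exposure, but every participant has been assessed by the committee, so that association cannot be estimated

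*Protocol article*

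**What the plan says.** The Statistical Analysis Plan section gives the purpose of the exploratory multivariable models as "to evaluate the association between multidisciplinary committee assessment and changes in pain intensity after adjustment for clinically relevant covariates". The ten candidate covariates are age, sex, cancer type, tumor stage, metastatic disease, and then "baseline VAS score, baseline opioid consumption, ongoing oncological treatment, interventional pain procedures, and palliative care status".

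Three other places fix who is exposed to the committee:

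- Inclusion Criteria requires "presentation to the multidisciplinary cancer pain management committee".
- Recruitment and Informed Consent places enrolment "during the first face-to-face visit to the pain unit following committee discussion".
- Strengths and Limitations opens its statement on causal inference with "Because of the observational pre-post design and the absence of a control group".

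Two further places bear on the covariates and on how the models will be read. The Recruitment section lists, among possible committee recommendations, "opioid rotation or dose adjustment, interventional pain procedures, referral for radiotherapy", and later in the same sentence palliative care interventions. Strengths and Limitations closes by saying that "residual confounding cannot be completely excluded despite planned exploratory adjusted analyses".

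**The concern.** A regression can estimate the association of an exposure with an outcome only if the exposure differs between the units analysed. Here the outcome is one change score per patient, and every patient has the exposure. The stated aim therefore asks for a quantity that the design does not contain.

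At stake is the labelling of a result. An analyst following the text would have to drop the committee term or report something else in its place, such as an intercept or an adjusted mean. Either could then be read as a confounder-adjusted committee association, although the protocol says in several places that no causal inference is possible.

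A second, smaller matter is the timing of one covariate. The baseline characteristics listed earlier in the same section include interventional procedures qualified as previous; the covariate list names them without that word. If procedures done after the committee meeting were entered, the model would condition on something that may follow from the committee's own recommendations.

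**Working it through.** The documents give no figure for this analysis, so there is none to reproduce. The check is one of identifiability.

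**1. Exposure.** Write C = 1 for a patient assessed by the committee and 0 otherwise. By the inclusion criterion, the timing of consent and the absence of a control group, C = 1 for all participants. The article describes no waiting period or graded exposure that could supply variation.

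**2. Model.** With one VAS change (T1 minus T0) per patient and covariates X:

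change = b0 + b1·C + g'X + error = (b0 + b1) + g'X + error, since C = 1 throughout.

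For any constant k, the pair (b0 + k, b1 - k) fits equally well. Only the sum b0 + b1 is identified. More patients do not change this.

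**3. Numerical check.** Simulated data, N = 64 (the number required under Sample Size and Power Calculations), with assumed coding of 5 cancer types and 4 stages:

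- Covariate columns: age 1, sex 1, cancer type 4, stage 3, metastatic disease 1, baseline VAS 1, baseline opioid 1, oncological treatment 1, procedures 1, palliative status 1 = 15.
- Total columns: 15 + intercept 1 + committee 1 = 17.
- Rank of the design matrix: 16, one short.

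The shortfall of one comes from the committee column and does not depend on the assumed coding.

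**4. Can another reading supply the association?**

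- *Intercept as the adjusted result.* A least-squares fit with an intercept passes through the means, so with mean-centred covariates the intercept equals the raw mean change. Simulation: -1.3096 against -1.3096.
- *Time (T0 or T1) as the exposure, two rows per patient.* With complete pairs and covariates fixed over time, the time coefficient is again the mean change. Simulation: -1.3096. Adjustment adds nothing to the paired comparison.
- *Implementation status (Table 2).* This does vary between patients, but it is listed as a separate exploratory variable and is not the exposure named in the aim.

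**5. What can be estimated.** The coefficients g, that is, how VAS change varies with patient and disease characteristics. Because baseline VAS is a candidate covariate, modelling the change or modelling T1 VAS gives the same coefficients for all other covariates in any linear model that includes it; only the baseline VAS coefficient shifts, by 1.

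**6. Covariate timing.** Nine of the ten candidate covariates repeat the baseline list in the same section; baseline VAS is the addition. The word previous is absent from the procedures item. To illustrate why timing matters, the simulation gave procedures an assumed effect of -1 point in about half of the patients. Reading the intercept at no procedure moved the mean change from -1.31 to -0.91, a shift of 0.40. These are invented inputs and show direction only.

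**The case against.** The strongest reply is that this is one clause about a secondary model. The section calls the adjusted models hypothesis-generating, and the Abstract, Objectives and Discussion all disclaim causal inference. The same sentence begins from the premise that patient and disease characteristics may influence pain, and those associations are estimable. All of this stands. It limits the seriousness of the point, but a label of exploratory describes the strength of evidence and cannot make a constant exposure estimable. Nor can a fuller analysis plan repair it, because the article itself states the target.

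Several stronger readings are tempting and are not supported:

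- A reader might infer that the model adjusts for committee-recommended procedures. The documents do not say so. The covariate list otherwise closely follows the baseline list, and previous may simply have been dropped. Only the ambiguity is established.
- A reader might infer that the model is overfitted. Under the assumed coding, 64/15 = 4.3 patients per covariate parameter, but the number of levels is not given, the variables are only candidates, and selection is commonly left to the full plan.
- A reader might infer that the limitations section claims that adjustment reduces confounding of a committee effect. It makes no such statement; the word despite merely invites the inference.
- A reader might predict that an intercept will be published as a committee effect. The protocol's own disclaimers point the other way.

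**Conclusion.** The point holds in this form: the stated aim of the exploratory regression names an exposure that is constant by design, so its association with pain change cannot be estimated. Adjustment can return only the pre-post mean change or the associations of the covariates. This conclusion rests on the eligibility criteria, the timing of consent and the absence of a control group, and on no numerical assumption.

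The timing of interventional procedures and of palliative care status is left open and should be settled; nothing shows that post-committee values are intended.

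This should be fixed, but it is not a fundamental flaw. A reader might infer that the study's main result is compromised. It is not: the paired T0-T1 comparison of VAS and the sample size built on it do not use this model.

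**What to change.** In Statistical Analysis Plan, delete the wording about an association with committee assessment and state an aim that the data can meet, for example: *Exploratory linear regression will examine which patient and disease characteristics recorded at T0 are associated with the change in VAS score from T0 to T1, adjusting for T0 VAS.* Modelling T1 VAS adjusted for T0 VAS is an equivalent choice.

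In the covariate list, state that interventional procedures means those performed before T0, matching the baseline list, and that palliative care status is its state at T0.

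In Strengths and Limitations, replace the reference to adjusted analyses with wording such as: *The adjusted models describe how pain change varies with patient characteristics; without an unexposed group they do not control confounding of a committee effect.*

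The cost is a few sentences, with no new data and no change to the primary analysis or sample size. With 3 participants enrolled when the article was submitted, the amendment can be made and the registration updated before many T1 outcomes exist. What is given up is only the wording of an adjusted committee association, which the design could not have delivered.
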